**Exclusion criteria**

Registered patients will be excluded from the data extract if they have expressed a wish to be excluded from the surveillance programme.

Logical checks will be performed and patients identified with nonsensical records will be excluded. Those with unusual COVID-19 vaccine histories will be excluded.

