**Exclusion criteria**

- Logical checks will be performed and patients identified with nonsensical records will be excluded.
- Those with unusual COVID-19 vaccine histories (vaccination outside the campaign period or receiving an alternative vaccine to the main offer – see section 3.5).
- SARS-CoV-2 negative controls with a positive influenza test will be excluded for analyses that span the main period of influenza circulation (i.e. Autumn booster evaluations, but not Spring booster evaluations).
- Patients swabbed >10 days post onset.
- Patients whose swab date cannot be determined.
- Patients with no linked vaccination history or clinical risk status.

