**3.4 Study period**

This proposal relates to an ongoing programme of disease surveillance. Data are collected continuously on a daily basis in England. It includes the diagnoses or problems reported at every consultation. The database can be interrogated in relation to any specific disease or in any defined period. It is assumed that the period of COVID-19 activity will continue throughout 2023 and 2024, this will be monitored through surveillance.

Autumn 2022 booster vaccine doses were offered to all age 50+ plus all members of clinical risk groups age 5+ and health and social care workers, carers or close contacts of the immunosuppressed. Autumn booster doses primarily included bivalent Original/Omicron BA.1 mRNA vaccines (Pfizer-BioNTech, Comirnaty or Moderna, Spikevax). The autumn booster vaccination campaign opened 5 September 2022 and closed 12 February 2023.

Spring 2023 boosters were offered to those age 75+ or those with weakened immune systems, during the period 3 April – 30 June 2023. Vaccines given were primarily either bivalent Original/Omicron BA.4-5 mRNA vaccines (Pfizer-BioNTech, Comirnaty) or monovalent Beta recombinant vaccines (Sanofi-GSK, VidPrevTyn).

From Autumn 2023, a new booster vaccine dose will be offered to all age 50+ plus all members of clinical risk groups age 5+ and health and social care workers, carers or close contacts of the immunosuppressed. Autumn booster doses will include monovalent XBB mRNA vaccines, bivalent Original/Omicron BA.4-5 mRNA vaccines, and monovalent Beta recombinant vaccines, depending on age and availability. The autumn booster vaccination campaign will be ongoing from September 2023.

The data may be examined in any arbitrary period according to interest. At the time of writing, Omicron XBB lineages are dominant, but this could change at any time, and variant may impact vaccine effectiveness. Study periods may be amended to cover variant-dominant periods of infection or according to decision makers needs. Cohort analyses may require censoring at the last date in records where outcomes appear to be well captured.

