**Ascertainment**

Vaccination status, date, manufacturer and type is extracted from the study database (and linked from other sources if necessary).

Individuals will contribute pre-booster person time up to the point of booster vaccination and thereafter assigned to categories based on combinations of time since dose and booster vaccination type

Time since dose:

- pre-booster/unboosted (baseline)
- 0-13 days,
- 14-91 days,
- 92-182 days,
- 183+ days

Type of vaccine:

- mRNA XBB
- mRNA bivalent original/BA.4-5
- recombinant Beta

These categories may be assigned separate factors for different manufacturers, as required.

The following are considered ‘odd’ vaccination histories, to be considered for exclusion:

- Other vaccine types than those listed in section 3.4 above
- Vaccination between 13 February and 3 April 2023 (for Spring 23 booster analysis)
- Vaccination between 31 June and 3 Sept 2023 (for Autumn 23 booster analysis)

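### The odd-vaccination-history exclusion is not tied to study entry or swab date, is mandatory in one section and optional in another, and has two faulty window dates

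*Protocol*

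**What the plan says.** Section numbers refer to the COVID-19 study in the protocol.

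- Section 3.2.1 (cohort): "Those with unusual COVID-19 vaccine histories will be excluded". The term is not defined there.
- Section 3.2.2 (test-negative design, TND) lists the same exclusion, describes it as "vaccination outside the campaign period or receiving an alternative vaccine to the main offer", and refers to section 3.5.
- Section 3.5 softens the rule to "vaccination histories, to be considered for exclusion" and gives three criteria. The first has no date: "Other vaccine types than those listed in section 3.4 above". The other two are windows, each assigned to one analysis: "Vaccination between 13 February and 3 April 2023 (for Spring 23 booster analysis" and "Vaccination between 31 June and 3 Sept 2023 (for Autumn 23 booster analysis".
- Section 3.4 puts the Autumn 2022 campaign at 5 September 2022 to 12 February 2023, with analysis to 2 April 2023. Spring boosters were offered "during the period 3 April – 30 June 2023", with analysis from 3 April to 3 September 2023. The Autumn 2023 analysis starts with that programme, in September 2023.
- Exposure varies with time in the cohort and is fixed at the swab in the TND (sections 3.5 and 3.12). The only censoring mentioned concerns completeness of outcome capture (section 3.4).

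**The concern.** Exposure is assigned as time passes, but eligibility is not. Nothing limits the exclusion to doses already given when a person enters follow-up or is swabbed. Both the Autumn 2022 and Spring 2023 analyses outlast their campaigns and are run retrospectively, so later doses will be in the extract. Section 3.4 also says that the named products were only the main ones used, so an unlisted product given during a campaign is foreseeable.

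If such a person is dropped entirely, the unboosted time before the odd dose goes too. For the death outcome that time contains no deaths, because the person had to be alive to receive the dose. Removing it raises the unboosted death rate and flatters the vaccine.

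Separately, an analyst cannot tell whether exclusion is required or optional, and two window dates do not fit the campaign dates.

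**Working it through.** The documents give no count or rate of odd histories, so there is no stated figure to reproduce. The check covers the dates, then the direction and size of any bias.

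**Dates.**
- Autumn 2022 analysis, 5 September 2022 to 2 April 2023: 26+31+30+31+31+28+31+2 = 210 days. After campaign close, 13 February to 2 April: 16+31+2 = 49 days.
- Spring 2023 analysis, 3 April to 3 September: 28+31+30+31+31+3 = 154 days. After campaign close, 1 July to 3 September: 31+31+3 = 65 days.
- June has 30 days, so 31 June does not exist. The first off-campaign day after 30 June is 1 July.
- The Spring window ends on 3 April, which is the first day of both the Spring campaign and its analysis. Read inclusively, it flags valid opening-day recipients as odd.
- Apart from that day, both windows end before the analysis they belong to, so they act as baseline exclusions. No window is listed for Autumn 2022.

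**Cohort, death outcome.** If a share f of unboosted person-time is removed with no deaths in it, the unboosted rate is multiplied by 1/(1−f), so observed VE = 1 − (1−VE)(1−f).

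| f (assumed) | true VE 30% | true VE 60% |
| --- | --- | --- |
| 1% | 30.7% | 60.4% |
| 5% | 33.5% | 62.0% |
| 10% | 37.0% | 64.0% |

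For example, 1 − 0.70 × 0.95 = 0.335.

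**How f could arise (Spring 2023, 154 days).** Assumptions: 60% boosted evenly over days 0–89 (mean 44.5), and a share q of the other 40% given an odd dose evenly over days 89–154 (mean 121.5). Ignoring the few deaths,

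f ≈ 0.4q × 121.5 / [0.6 × 44.5 + 0.4(1−q) × 154 + 0.4q × 121.5].

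For q = 1% this is 0.486/88.17 = 0.55%. A day-by-day calculation with deaths, using the 1% attack rate of section 3.10 purely for illustration, gives f = 0.55%, 2.76% and 5.56% for q = 1%, 5% and 10%. A true VE of 30% then reads 30.4%, 31.9% and 33.9%. If the odd dose is instead an unlisted product given during the campaign, 30% reads 30.1% at q = 1% and 30.7% at q = 5%. Censoring at the odd dose returned the true VE in every case.

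**TND.** If a share a of unboosted cases and b of unboosted controls is removed, observed VE = 1 − (1−VE)(1−b)/(1−a). With a = b there is no bias. For a true VE of 30%:
- a = 2%, b = 5%: 1 − 0.70 × 0.95/0.98 = 32.1%
- a = 5%, b = 2%: 1 − 0.70 × 0.98/0.95 = 27.8%

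**The case against.** The strongest reply is that section 3.5 supplies the definition, and its dated windows are tied to the following campaign's analysis. A dose in August 2023 is listed as odd for Autumn 2023, not for Spring 2023. Section 3.5 also only proposes that exclusion be considered, and nowhere does the protocol say that doses after entry or after the swab count. The time anchor of an exclusion flag could be settled in an analysis plan that is not shown.

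Much of this stands. A reader might infer that the plan certainly discards people for later off-campaign doses and that VE is therefore biased. The documents do not support that. Reaching that result for off-campaign doses requires reading the parenthesis in section 3.2.2 without its cross-reference, and extending it to the cohort.

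A reader might also infer a large effect. With 70% boosted after a mean of 35 days, odd doses at a mean of 121 days and a true VE of 40%, giving 5% of all eligible people an odd dose makes VE read 45.3%. But that means 5/30, or about 17%, of those not boosted in the campaign, and nothing in the documents suggests such a figure. Nor is the 1% change in section 3.12 a yardstick here: it governs which covariates to retain, not how much bias is tolerable.

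The reply does not remove three things. The vaccine-type criterion has no date in any analysis. Sections 3.2.1 and 3.5 disagree on whether exclusion is mandatory. And the two window dates are faulty as printed.

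**Conclusion.** The point holds as a defect of specification with a limited risk of bias. The rule has no time anchor and is not consistently mandatory. One window starts on an impossible date. The other overlaps the first Spring day if read inclusively.

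Followed literally, the vaccine-type criterion can select cohort members on a later dose. So can the general off-campaign wording, if used in the 49-day and 65-day tails. For death, the resulting error in VE is upward. This assumes that the person was unboosted until the odd dose; for someone already boosted in the campaign, boosted time would be lost as well, which works the other way.

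The size depends on a frequency that the documents do not give. In the cohort calculation above, a true VE of 30% shifts by less than half a point when 1% of people not boosted in the campaign have an odd dose, and by about 2 points at 5%. For hospitalisation the direction is less certain, because an admitted person can still be vaccinated later. In the TND there is bias only if removal differs between cases and controls, with no fixed sign.

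**What to change.** 1. Apply the exclusion only to odd doses dated before the start of follow-up (cohort) or before the swab (TND).
2. For a later odd dose, keep the cohort member and censor person-time at that dose. In the TND, ignore doses after the swab.
3. Make sections 3.2.1, 3.2.2 and 3.5 agree on whether exclusion is mandatory, and use one definition.
4. End the Spring 2023 window on 2 April 2023 and start the Autumn 2023 window on 1 July 2023, in line with the campaign dates in section 3.4.
5. State what applies to Autumn 2022: the same censoring rule for doses after 12 February 2023.

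The cost is a few lines of protocol text and one censoring step in the code. No new data are needed, and slightly more person-time is retained. A count of odd doses by date relative to entry or swab would show whether the issue matters in practice.

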**GP computerised databases**

Individual-level data is extracted twice-weekly from GP computer systems into the RCGP RSC database. SNOMED clinical terms^[[4]](#footnote-4)^ are used to identify outcomes, risk factors, cases of COVID-19 and vaccination events.^[[5]](#footnote-5)^ Routines to extract and manipulate the data into the correct format for statistical analysis are required.

**3.2.2 TND study population**

**Definition**

The TND study population is composed of individuals that have contented to a respiratory swab as part of the sentinel swabbing scheme.

**Exclusion criteria**

- Logical checks will be performed and patients identified with nonsensical records will be excluded.
- Those with unusual COVID-19 vaccine histories (vaccination outside the campaign period or receiving an alternative vaccine to the main offer – see section 3.5).
- SARS-CoV-2 negative controls with a positive influenza test will be excluded for analyses that span the main period of influenza circulation (i.e. Autumn booster evaluations, but not Spring booster evaluations).
- Patients swabbed >10 days post onset.
- Patients whose swab date cannot be determined.
- Patients with no linked vaccination history or clinical risk status.

**3.3 Study setting**

| **Cohort**  Total number of practices: ~1800,  Size of population: ~18,800,000 registered persons (all patients registered in the practices).  Representativeness: The population is closely representative of the English national population by region and by age and gender. The population is about one third of the national population.  For practical purposes this is a complete database of information collected in the sentinel networks. Given the programme of enhanced data extraction which is underway we would not expect to lose more than 2% of relevant data.  The practice data bases are an accumulated record of person-specific health-related data. We extract selected data to provide our routine surveillance program. |
| --- |

| ***TND***  Participants in the RCGP/UKHSA sentinel swabbing scheme. These are patients who contacted their GP, where the GP was part of the Royal College of General Practioners Research and Surveillance Centre (RCGP-RSC) sentinel scheme, and who had a sentinel respiratory swab taken with a result for SARS-CoV-2. >200 practices contribute sentinel swabs for virology.  Indications for swabbing are influenza-like illness, COVID19-like illness, an acute respiratory infection or exacerbation of asthma/COPD with onset within the last 10 days.  Patients are either swabbed and consented by their GP as part of a face-to-face consultation, or directed to take a postal self-swab by GPs through takeatestuk.com after being issued a voucher code.  All sentinel swabs are tested for respiratory infections including influenza and RSV using RT-PCR at UKHSA’s Virus Reference Laboratory. Vaccination data are available via linkage to GP records. |
| --- |

**3.4 Study period**

This proposal relates to an ongoing programme of disease surveillance. Data are collected continuously on a daily basis in England. It includes the diagnoses or problems reported at every consultation. The database can be interrogated in relation to any specific disease or in any defined period. It is assumed that the period of COVID-19 activity will continue throughout 2023 and 2024, this will be monitored through surveillance.

Autumn 2022 booster vaccine doses were offered to all age 50+ plus all members of clinical risk groups age 5+ and health and social care workers, carers or close contacts of the immunosuppressed. Autumn booster doses primarily included bivalent Original/Omicron BA.1 mRNA vaccines (Pfizer-BioNTech, Comirnaty or Moderna, Spikevax). The autumn booster vaccination campaign opened 5 September 2022 and closed 12 February 2023.

Spring 2023 boosters were offered to those age 75+ or those with weakened immune systems, during the period 3 April – 30 June 2023. Vaccines given were primarily either bivalent Original/Omicron BA.4-5 mRNA vaccines (Pfizer-BioNTech, Comirnaty) or monovalent Beta recombinant vaccines (Sanofi-GSK, VidPrevTyn).

From Autumn 2023, a new booster vaccine dose will be offered to all age 50+ plus all members of clinical risk groups age 5+ and health and social care workers, carers or close contacts of the immunosuppressed. Autumn booster doses will include monovalent XBB mRNA vaccines, bivalent Original/Omicron BA.4-5 mRNA vaccines, and monovalent Beta recombinant vaccines, depending on age and availability. The autumn booster vaccination campaign will be ongoing from September 2023.

The data may be examined in any arbitrary period according to interest. At the time of writing, Omicron XBB lineages are dominant, but this could change at any time, and variant may impact vaccine effectiveness. Study periods may be amended to cover variant-dominant periods of infection or according to decision makers needs. Cohort analyses may require censoring at the last date in records where outcomes appear to be well captured.

To evaluate the Autumn 2022 boosters, analyses will commence Monday 5 September 2022 and end Sunday 2 April 2023. We note that dominance of variants shifted from Omicron BA.5 at the beginning of this period, to Omicron BQ.1 from w/c 7 November 2022, to co-circulating Omicron XBB, XBB.1.5 and CH.1.1 from w/c 23 January 2023 with XBB.1.5 prevailing from w/c 20 February 2023, hence secondary analyses will explore splitting the study period accordingly.

To evaluate the 2023 Spring boosters, analyses will start on the Monday 3 April and end Sunday 3 September. Evaluation will occur September 2023, or as soon as linked data are available. Omicron XBB.1.5 was the dominant variant at the beginning of the study period.

To evaluate the 2023 Autumn boosters, cohort and TND analyses will start on the Monday of the first week of the booster programme. The TND analyses will be in conjunction with influenza VE, in January and May 2024. Evaluation via the cohort will be after the end of the influenza season.

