**2.2 Primary objectives**

The key questions to be addressed for confirmed COVID-19 infection and clinical outcomes in 2023/24 in relation to vaccine effectiveness, taking into account previous vaccination and booster vaccination, will be to estimate:

- Overall VE by vaccine type (mRNA or other)
- VE by specific clinical risk group
- VE by time since vaccination
- VE by time period, depending on the timing of boosters and circulation of specific variants

| Outcomes combine confirmed and clinical elements:  **Confirmed**: Swab either taken   - via GP from persons presenting with COVID-like symptoms. Laboratory investigation undertaken in the PHE Respiratory Virus Reference laboratory to detect positive swab for SARS-CoV-2 and other respiratory viruses.   **Clinical:**   - COVID-19 coded hospitalisation - COVID-19 coded death - death within 28 days of positive SARS-CoV-2 test. |
| --- |

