**3. Methods**

**3.1 Study designs**

For 2023/24 RCGP RSC and UKHSA in collaboration will use two main study designs to estimate COVID-19 vaccine effectiveness in England across all age groups, and in sub-populations for individuals registered with participating GPs in the RCGP RSC sentinel network. The primary designs to be used are as follows:

- Cohort study with primary outcomes hospitalisation and death.
- Test-negative design (TND) study on patients within the sentinel swabbing scheme.

This proposal covers both the cohort study and the TND study.

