**Antigenic drift / emergence of new strains**

Comparisons of V/E by time period will also inform this.

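### The variant-period split cuts cohort follow-up at variant-dominance weeks and makes no allowance for the delay from infection to admission or death

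*Protocol*

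**What the plan says.** Section 3.4 of the Protocol sets the period: "To evaluate the Autumn 2022 boosters, analyses will commence Monday 5 September 2022 and end Sunday 2 April 2023". It names three later changes in circulation. BA.5 gave way to BQ.1 in the week of 7 November 2022. The second change was "to co-circulating Omicron XBB, XBB.1.5 and CH.1.1 from w/c 23 January 2023". In the third, dated to the week of 20 February 2023, XBB.1.5 took the lead. The consequence drawn is "hence secondary analyses will explore splitting the study period accordingly".

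Section 2.2 lists "VE by time period, depending on the timing of boosters and circulation of specific variants" among the primary objectives. Section 3.1 names the first design as "Cohort study with primary outcomes hospitalisation and death". Section 3.12, under All studies, allows stratification by variant period as needed, which covers the cohort and the test-negative design (TND) alike. In section 4.6, on antigenic drift, the Protocol says "Comparisons of V/E by time period will also inform this".

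The cohort model in section 3.12 uses calendar week as a time-varying covariate and person-time in days. No section moves the variant cuts for admissions or deaths, assigns events by infection or test date, or leaves a gap after a cut. Section 3.4 also permits study periods to be amended toward variant-dominant periods of infection, but sets no rule for doing so.

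**The concern.** The cut dates describe what was circulating. A cohort event is dated by admission or death. If the study period is split at those dates, an infection acquired before a cut but leading to admission or death after it counts in the later window. The shorter the window and the longer the delay, the larger that share, so deaths in the two windows after 23 January 2023 are the most exposed.

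At stake is the comparison of VE between variant periods. Carry-over pulls each window's VE toward that of the window before. If VE falls when a new variant arrives, the fall is understated, most of all for death. The problem is which variant period an event is credited to. It is separate from the time-since-dose bands.

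**Working it through.** **Window lengths, from the section 3.4 dates.** 5 Sep to 6 Nov 2022 is 63 days, 7 Nov to 22 Jan is 77, 23 Jan to 19 Feb is 28, and 20 Feb to 2 Apr 2023 is 42. The sum is 63 + 77 + 28 + 42 = 210 days, the whole period. If the last two are read as one period, it has 28 + 42 = 70 days.

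**Delays.** The Protocol gives none. Its nearest figures are bounds in section 3.6: a positive test up to 14 days before admission (secondary-code route only), and death within 28 days of a positive test (secondary definition only). It does not say whether the dominance weeks are dated by infection, specimen or report. Assumed mean lags are therefore 14-28 days to death and 7-10 days to admission. If the dominance weeks are specimen-dated, 3-5 days to admission is assumed.

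**Share infected before the window opened.** With flat incidence, lag L and window length W, the share is E[min(L, W)] / W. When L seldom exceeds W this is close to mean lag / W, for example 7/28 = 25% and 10/42 = 24%. Gamma lags with coefficient of variation (CV) 0.5 to 0.6 give:

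| Mean lag (days) | 28-day window | 42-day window | 70-day window |
|---|---|---|---|
| 3 | 11% | 7% | 4% |
| 5 | 18% | 12% | 7% |
| 7 | 25% | 17% | 10% |
| 10 | 36% | 24% | 14% |
| 14 | 48-49% | 33% | 20% |
| 21 | 66-68% | 48-49% | 30% |
| 28 | 77-80% | 61-63% | 40% |

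In the 77-day window the shares are 9-13% for admissions (7-10 days) and 18-36% for deaths. With infections rising 25% or falling 20% a week, the share of deaths in the 28-day window runs from 34% to 90% (gamma, CV 0.6).

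**Effect on VE in the 28-day window.** Assume VE of 50% against the old variant and 30% against the new. If a fraction p of reference-group events is due to the new variant, pooled RR = 0.5(1 - p) + 0.7p, so VE = 50 - 20p (in percent).

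Assume logistic takeover with 50% new variant at the cut and growth g of 0.03 to 0.10 per day. With perfectly infection-dated windows, p = ln[(1 + e^(28g))/2] / (28g).
- g = 0.10: p = ln(8.72)/2.8 = 0.774, VE = 34.5%.
- g = 0.03: p = ln(1.658)/0.84 = 0.602, VE = 38.0%.

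For lagged events, p is averaged over infection times (event time minus a gamma lag, CV 0.5). The increase in VE over the infection-dated value is:
- deaths: about 2-5 points at a mean lag of 14 days, 3-8 at 21 and 4-10 at 28;
- admissions: about 1-4 points at 7-10 days, and under 2 at 3-5 days.

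**The case against.** **The analysis is secondary and exploratory, and a lag could be left to a statistical analysis plan.** That limits the weight of the point. But the Protocol itself names the dates and says the period will be split at them. The same dates serve every outcome, so an analyst who follows the text will misdate part of the cohort events. That the cuts apply to admissions and deaths is inferred from sections 3.4 and 3.12 read together; it is not stated outright.

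**Section 3.4 points to periods of infection.** It does, and that is the right concept, but it is only a permission with no rule attached.

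**The four-window reading is a choice.** The last two windows can be read as one of 70 days. The carry-over then falls to 20-40% of deaths and, at 7-10 days, 10-14% of admissions. It is smaller but still present.

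**Infection before a cut is not previous-variant infection.** This stands. A reader might infer that the shares above are events from the previous variant, and hence that the 28-day window would report 30 + 20 × 0.48 = 40% to 30 + 20 × 0.80 = 46% where 30% is true. The Protocol does not support that. Its cuts mark changes of dominance, not replacement, and the 28-day window is described as co-circulation that already includes XBB.1.5. Part of the carry-over into the 42-day window is therefore XBB.1.5 itself. Under gradual takeover even infection-dated windows give 34.5-38%, and no lag rule removes that part.

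**Conclusion.** The point holds for the cohort's variant-period analyses. The cuts follow circulation, the outcomes are delayed, and nothing allows for the delay. Under the assumed lags, carry-over into the short windows is substantial for deaths and modest to moderate for admissions. The direction is toward the earlier period's VE, by roughly 2-10 points for death and 1-4 for admission in the 28-day window. These sizes depend on assumed delays, flat incidence, an illustrative VE contrast of 50% against 30% and an assumed takeover speed. The carry-over shares are upper approximations to previous-variant events.

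A reader might extend this to the main results, but the documents do not support that. Whole-period VE uses no internal variant cut. The TND is dated by swab, taken within ten days of onset, so the delay to admission or death does not arise there. The change is worth making before the split is run, but it does not threaten the primary estimates.

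**What to change.** For the cohort variant-period analyses, state an outcome-specific lag and shift the cut dates by it, for events and person-time alike. Estimate the lag from the linked test-to-admission and test-to-death intervals; Table 1 in section 3.9 already lists the dates of positive test, admission and death. State how the dominance weeks are dated and, if not by specimen, add an explicit allowance for infection to test. Alternatively, drop a washout of that length at the start of each window. Report sensitivity to the chosen lag, and leave the TND windows as they are.

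Handle the period end explicitly. With a 21-day shift, for example, the last cut moves from 20 February to 13 March 2023, which leaves 21 of the 42 days before 2 April. Extending beyond that date runs into the Spring 2023 evaluation, which starts on 3 April.

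The cost is small: different cut dates by outcome in the same code and no new data. A washout loses events. At 21 days it leaves 28 - 21 = 7 days of the 28-day window, and at 28 days none, so shifting is the better choice for deaths. Two limits remain. The lag is estimated only in people with a test, because the primary-code admission route and the primary death definition require none. And a fixed shift reduces carry-over from a variable delay without removing it.
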